#### Main Analyses

The primary outcome, that is, change in social anxiety, will be tested using Linear Mixed Effects Models. Time (baseline, midintervention, post intervention, and follow-up), intervention condition (SOPHIE and CAU), diagnostic status (SAD and subclinical social anxiety), and interactions (time*intervention condition; time*diagnostic status; intervention condition*diagnostic status; time*intervention condition*diagnostic status) will be specified as fixed effects, baseline SPIN value will be added as a fixed covariate and participant as a random effect to allow for between-person variation.

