**Methods:**

A total of 222 adolescents aged 11-17 years with subclinical social anxiety (N=166) or with a diagnosis of social anxiety disorder (N=56) are randomly assigned to the online intervention or a care-as-usual control group. The 8-week guided online intervention is based on the Cognitive Model of Social Phobia and evidence-based online interventions for social anxiety adapted to the specific needs of adolescents. The care-as-usual group will be given access to the online intervention after the follow-up assessment. Participants are assessed at baseline, at 4 and 8 weeks post intervention, and at 3-month follow-up assessment on the primary outcome, that is, social anxiety, on secondary outcomes (eg, level of functioning, fear and avoidance, general anxiety, depression, quality of life, self-esteem, and negative effects of the intervention), on potential moderators (eg, therapy motivation, therapy expectancy, and satisfaction with the intervention), and potential mediators (eg, therapeutic alliance and adherence to the intervention). Data will be analyzed based on an intention-to-treat approach and both groups (intervention and care-as-usual) will be compared at each assessment time point. Furthermore, potential mechanisms of change and generalization of intervention effects on daily life are assessed using an ecological momentary assessment procedure that includes items on maintaining mechanisms of social anxiety, social context, and affect. Participants are prompted 3 times a day during the first 8 weeks of the study and again for 2 weeks following the follow-up assessment.

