The primary objective of this study is to examine the efficacy of an online intervention called SOPHIE for adolescents with subclinical social anxiety or SAD compared to a care-as-usual (CAU) control group. Thereby, the name SOPHIE is derived from the German term “SOziale PHobIE” (social phobia). It is hypothesized that SOPHIE will be superior to CAU in reducing social anxiety symptoms post assessment and that the intervention effect will be maintained until follow-up assessment 3 months after intervention completion. Furthermore, it is hypothesized that SOPHIE will also have beneficial effects on secondary outcomes, such as depressive as well as general anxiety symptoms, level of functioning, self-esteem, and quality of life at post assessment and follow-up. It is further hypothesized that intervention effects will be moderated by therapeutic alliance, adherence, treatment motivation, and treatment expectation of the online intervention. Moreover, by measuring social anxiety symptoms in their natural context longitudinally, we will examine if intervention effects translate into everyday life and if the postulated maintaining factors of SAD function as mediators of change. Additionally, we intend to model the network structure of social anxiety symptoms at each time point and observe differences in networks of adolescents (eg, regarding age, gender, and severity of social anxiety).

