## Methods

### Study Design

This randomized controlled trial (RCT) investigates the efficacy of the online intervention SOPHIE for adolescents with subclinical social anxiety or a diagnosis of SAD. SOPHIE is compared to a CAU control condition in a 2×2×4 design with a 2-level between-subjects factor (2 experimental conditions: SOPHIE vs CAU), a 2-level between-subjects factor (2 diagnostic conditions: SAD vs subclinical social anxiety), and a 4-level within-subjects factor (repeated measures: baseline, midintervention at week 4, post intervention at week 8, and follow-up 5 months after randomization, ie, 3-months follow-up). All participants are additionally assessed in EMA surveys during the first 8 weeks (from baseline to postassessment) and for 2 weeks after follow-up assessment. Participants in the intervention group have additional process assessments at weeks 2 and 6 during the intervention.

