### Outcome Measures

#### Primary and Secondary Outcomes

The primary outcome is the severity of social anxiety assessed by the SPIN [67]. The National Institute of Health and Care Excellence guidelines recommend the SPIN as a screening and assessment instrument suited for adolescents [23]. Please see Table 1 for a detailed description and assessment points of the primary and secondary outcomes: social anxiety, social and role functioning, utilization of help, anxiety, depression, quality of life, self-esteem, therapy expectation, therapy motivation, negative effects of the intervention, satisfaction with the intervention, therapeutic alliance, and adherence to the intervention.

**Table 1 table1:** Overview of assessments and assessment points during the SOPHIE study.

Construct		Description of assessment	Timeline of assessment					
			Baseline	Week 2	Midintervention or control at week 4	Week 6	Postintervention or control at week 8	Follow-up at week 20

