#### Further Analyses

Secondary outcomes (ie, global functioning, general anxiety symptoms, depressive symptoms, quality of life, self-esteem, and guardians’ rating of their child’s social anxiety) will be analyzed using Linear Mixed Effects Model as described earlier. In further analyses, therapy expectancy, therapy motivation (both adolescents’ and guardians’), and satisfaction with the intervention will be added as moderators. Categorical outcomes (eg, diagnostic status) will be analyzed using General Linear Mixed Effect Models with intervention condition, diagnostic status, and time course as fixed effects and participants as random effect. Additionally, Growth Mixture Modeling will be used to identify subpopulations with comparable growth trajectories of social anxiety and secondary outcomes over time (latent classes) and to identify predictors of these classes.

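### Baseline SPIN is both an outcome level and a covariate in the primary model, so the change contrast gains no precision and visit-wise group comparisons run at about 8% error instead of 5%

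*Protocol article*

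**What the plan says.** Main Analyses in the protocol article lists the fixed effects of the linear mixed model for SPIN as "Time (baseline, midintervention, post intervention, and follow-up), intervention condition (SOPHIE and CAU), diagnostic status (SAD and subclinical social anxiety), and interactions", and then adds that "baseline SPIN value will be added as a fixed covariate and participant as a random effect to allow for between-person variation". Study Design confirms that baseline belongs to the response: the design has a "4-level within-subjects factor (repeated measures: baseline, midintervention at week 4, post intervention at week 8, and follow-up 5 months after randomization".

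On which comparisons will be made, the Introduction hypothesises that "SOPHIE will be superior to CAU in reducing social anxiety symptoms post assessment", with the effect maintained to follow-up. Main Analyses describes the primary outcome as change in social anxiety. The Methods paragraph of the Abstract says that "both groups (intervention and care-as-usual) will be compared at each assessment time point". Further Analyses says that the secondary outcomes "will be analyzed using Linear Mixed Effects Model as described earlier".

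Nothing in the article removes baseline from the response or sets the arms equal at baseline.

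**The concern.** Baseline adjustment in a randomised trial serves to remove prognostic noise from the treatment comparison. It does so when baseline is on the right-hand side only, or when it is a response with the arms constrained to a common baseline mean. Here it is on both sides without the constraint. What follows depends on the contrast that is read from the model:

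- **Change from baseline (time by condition).** A covariate that is constant within a participant and has no interaction with time cannot affect a within-participant difference. The adjustment would be reported but would do nothing.
- **Group difference at a visit.** One slope is fitted to all four occasions, and on one of them the covariate equals the response. The slope is pulled upward, the random-intercept variance shrinks, and the model understates the variance at post-baseline visits. The stated 5% level would not hold.

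**Working it through.** **Inputs.** From Sample Size: r=0.4, α=5%, d=0.35 (SAD, 56 participants) and d=0.20 (subclinical, 166), total 222. From Procedures: allocation 1:1, hence n=111 per arm. Assumptions: SPIN variance 1 at each visit, the same correlation r between any two visits (compound symmetry, which matches the single r and the random intercept), and no allowance for the screening cutoff of 16.

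**The plan's own figure.** For a repeated-measures ANOVA with f=d/2, two groups, m measurements, λ=f²Nm/(1−r) and degrees of freedom m−1 and (m−1)(N−2):

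- m=4, SAD: λ=0.175²×56×4/0.6=11.43, power 0.810 at N=56.
- m=4, subclinical: λ=0.10²×166×4/0.6=11.07, power 0.803 at N=166.
- m=3 would need 66 and 196; m=2 would need 80 and 238.

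The stated sizes therefore reproduce with four measurements, baseline included, on the group-by-time interaction. A test of the group main effect would need 144 and 434. Four response levels are the intended design, not loose wording.

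**(a) Change contrast.** Write Y_ij = cell mean + βB_i + u_i + e_ij, where B_i is baseline SPIN. In Y_i,week 8 − Y_i,baseline both βB_i and u_i cancel. In units of 2σ²/n:

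- stated model: 2(1−r)=1.20
- baseline as covariate only: 1−r²=0.84
- ratio: 1.20/0.84=1.43

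In SD units, SE=√(2×1.20/111)=0.147 against √(2×0.84/111)=0.123.

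**(b) Group difference at a post-baseline visit.**

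- Fitted slope: (1+3r)/4=0.55. The correct slope for a post-baseline value is r=0.40.
- Residual variance: 1−r=0.60.
- Variance of the participant mean given baseline: 0.55−0.55²=0.2475. Random-intercept variance: 0.2475−0.60/4=0.0975, against 0.40 without the covariate.
- Variance the model believes: 0.0975+0.60=0.6975.
- True variance of Y−0.55B: 1−2(0.55)(0.40)+0.55²=0.8625.
- SE ratio: √(0.6975/0.8625)=0.899.
- Two-sided type I error: P(|Z|>1.96×0.899=1.76)=7.8%.

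In SD units, the reported SE is √(2×0.6975/111)=0.112 and the true one √(2×0.8625/111)=0.125.

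| r | slope | SE ratio | type I error at a visit | change variance, stated vs covariate only |
|---|---|---|---|---|
| 0.3 (assumed) | 0.475 | 0.907 | 7.5% | 1.40 vs 0.91 |
| 0.4 (plan) | 0.550 | 0.899 | 7.8% | 1.20 vs 0.84 |
| 0.6 (assumed) | 0.700 | 0.886 | 8.3% | 0.80 vs 0.64 |
| 0.8 (assumed) | 0.850 | 0.875 | 8.6% | 0.40 vs 0.36 |

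**Simulation of the full factorial model** (REML, 56+166, no treatment effect, r=0.4, complete data, 3,000 replicates, week 8):

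| model | visit difference: empirical SD / mean SE / error | change contrast: empirical SD / mean SE / error |
|---|---|---|
| stated model | 0.126 / 0.112 / 8.3% | 0.149 / 0.147 / 5.4% |
| four visits, no covariate | 0.134 / 0.134 / 5.1% | 0.149 / 0.147 / 5.4% |
| baseline as covariate only | 0.124 / 0.123 / 5.4% | does not apply: baseline is not a response |

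With and without the covariate, the change estimates agreed to within 4×10⁻¹⁵. A separate simulation (8,000 replicates) gave 5.0% for the 3-df interaction test and 4.9% for week 8 versus baseline.

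**Dropout.** The article gives no rate. With an assumed 30% missing at random and r=0.4, the cancellation is no longer exact, but there is still no gain: empirical SD 0.159 with the covariate, 0.158 without. The visit-wise error is then 8.6%. The SE of the change contrast is about 3% too small (simulated error 5.7%, Monte Carlo SE about 0.4 points).

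**The case against.** The best defence is that the test the trial was sized on is sound. Main Analyses speaks of change, the hypothesis speaks of reducing symptoms, and the sample size reproduces from the four-level interaction. The covariate drops out of that test and its error rate stays at 5%. Measured against the plan's own power calculation nothing is lost; the 43% extra variance is relative to a better model that the plan did not choose. This stands: for the change contrast the point concerns wasted precision, not validity.

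The visit-wise comparisons rest on one sentence of the Abstract, which names no estimator and does not call them primary. That is also true. But the sentence commits to comparing the groups at each assessment, and this model is the only one described for SPIN. If the comparisons are taken from it, the inflation follows.

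It could also be said that an article condenses the full plan. Here the article spells out the time levels, every interaction, the covariate and the random effect, so the conflict lies in what is written, not in what is left out.

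**Conclusion.** The point holds, as something that should be fixed. Baseline SPIN is used twice. For the change contrast, the adjustment brings no precision: variance 1.20 instead of 0.84 at r=0.4, with the loss shrinking as r rises. For visit-wise group differences taken from this model, the SE is about 10% too small and the type I error about 8% instead of 5%. The figures rest on compound symmetry and, for the exact cancellation, on complete data.

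A reader might infer more, which the documents do not support:

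- *The primary interaction test exceeds 5%.* Under compound symmetry with complete data it does not. Larger errors at follow-up would need correlations that decay over time. The article gives only a single r, and that inflation would come from the random-intercept covariance, not from the double use of baseline.
- *The trial is already underpowered.* The stated sizes reproduce at 80% for the four-level interaction.
- *All secondary outcomes share the fault.* Read literally, Further Analyses carries over baseline SPIN as covariate, so the other scales would not predict themselves. The fault carries over only if each outcome's own baseline is used.

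**What to change.** Choose one role for baseline:

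1. Use weeks 4, 8 and follow-up as the response, with baseline SPIN and its interaction with time as covariates; or
2. Keep all four visits as the response, drop the baseline covariate, and constrain the arm means to be equal at baseline within each diagnostic stratum.

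Randomisation stratified by diagnosis justifies the constraint in option 2. That option also keeps the 2×2×4 design and the four-measurement basis of the sample size. Option 1 is as good statistically but needs a sentence in Study Design and Sample Size, because the response then has three levels. Make the same change for any secondary outcome whose own baseline is the covariate, and say in Further Analyses which baseline is meant.

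The cost is one changed model statement and a short amendment, with no new data. It should be settled before outcomes are compared between arms.

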### Procedures

Adolescents interested to take part in the study leave their email addresses on the study website [60]. They receive the participant study information by email and are asked to provide informed consent or assent (see Figure 1 for study flow). Participants younger than 14 years provide written assent, and their parent or guardian provides written consent. Participants 14 years or older provide consent on their own. Informed consents are accepted both on paper by mail and electronically as scans via email. Once the consent forms have been received, they are printed out and stored in analog form. Afterward, potential participants are screened for eligibility. Those with a score lower than 16 on the Social Phobia Inventory (SPIN) [61,62] are not included in the study but receive immediate access to the online intervention. The cutoff of 16 was chosen in reference to a previous study that showed good discrimination between healthy and subclinical adolescents [63]. Adolescents with a SPIN score of 16 or higher receive the remaining baseline questionnaires. Subsequently, they are interviewed by trained psychology graduate students via phone to ascertain whether they fulfill the diagnostic criteria for SAD or not. Those with a current diagnosis of SAD are assigned to the SAD group, while those with no current and no past SAD diagnosis are assigned to the subclinical social anxiety group. Training and weekly supervision of the graduate students are carried out by the first and last authors.

Participants are assigned to the intervention group or the control group by stratified block randomization to ensure that both groups are balanced regarding the diagnostic status: SAD or subclinical social anxiety. The randomization is carried out after all data collected by the diagnostic interview including diagnoses are entered into the electronic protocol form hosted on Qualtrics (Qualtrics XM) [64]. Randomization was set up before the start of the study by the first author (ie, number of groups, allocation ratio [1:1], and size of blocks). During the study, the allocation list was produced using an automated computer-generated random numbers table and was concealed from the investigators and the participants. After randomization, the intervention group receives immediate access to the online intervention.

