#### Sample Size

The sample size of 222 was determined in 2 a priori power analyses for the primary research question using G*Power [106] based on an intention-to-treat approach to account for possible dropouts and repeated measures ANOVA. In the SAD group, we expected a small to moderate effect size (Cohen *d*=0.35) [18,107], and for the group with subclinical anxiety, a small effect size (Cohen *d*=0.20) [38,108-110]. For both groups, we assumed an α level of 5%, power of 80%, and a correlation between measurements of *r*=0.4. Consequently, the SAD group should consist of 56 participants, and the subclinical social anxiety group of 166 participants.

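### The primary mixed model, read literally, assumes equal variances and one common correlation across unequally spaced visits while baseline SPIN is both outcome row and covariate, so visit-specific standard errors can be wrong, most of all at follow-up

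*Protocol article*

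**What the plan says.** Main Analyses in the protocol article lists the fixed effects in full: time, intervention condition, diagnostic status and all their interactions. Time has four levels, starting at baseline: "Time (baseline, midintervention, post intervention, and follow-up"). Baseline SPIN therefore enters as an outcome row. It also enters on the right-hand side: "baseline SPIN value will be added as a fixed covariate". One random component is named: "participant as a random effect to allow for between-person variation". No random slope, serial correlation or visit-specific variance is mentioned.

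Study Design gives the visits as "baseline, midintervention at week 4, post intervention at week 8, and follow-up 5 months after randomization"; the column heading in Table 1 reads "Follow-up at week 20". The Sample Size section plans on a repeated measures ANOVA with one common correlation of 0.4. Further Analyses carries the model over to the continuous secondary outcomes.

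**The concern.** A random intercept with independent, equal-variance residuals is compound symmetry. Weeks 0 and 20 are taken to correlate as strongly as weeks 4 and 8, and every visit is given the same variance. The design gives reason to doubt both. The gaps are 4, 4 and about 12 weeks, and SPIN is restricted at 16 or above at entry but not later. The double use of baseline adds a separate problem: once the covariate is in the model, the baseline row cannot share the residual variance of the later visits.

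One pooled within-person error then serves every time-by-condition contrast. The main hypotheses at the end of the Introduction are superiority at post and maintenance to follow-up, and the Abstract plans a group comparison at each assessment. These are visit-specific statements, so their standard errors depend directly on this structure.

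**Working it through.** **Inputs.** From the article: visits at weeks 0, 4, 8 and 20 (Table 1), 222 participants, 1:1 allocation, common r = 0.4, d = 0.35 (SAD) and d = 0.20 (subclinical). Assumed, because the article gives no SDs or visit-specific correlations: SD 1 at each visit unless stated, the correlation patterns below, complete data, a two-sided 5% test, diagnostic status left out.

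**Step 1: the plan's own figure.** Within-between interaction, 2 groups, m = 4 visits, f = d/2, λ = f²·N·m/(1 − r).
- SAD: 0.175² × 56 × 4 / 0.6 = 11.43 on 3 and 162 df; power 81.0%.
- Subclinical: 0.10² × 166 × 4 / 0.6 = 11.07 on 3 and 492 df; power 80.3%.

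Both 56 and 166 are reproduced, so planning and model share compound symmetry.

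**Step 2: change from baseline.** In balanced data the random-intercept model estimates the within-person error as W = mean variance − mean covariance and gives every change score variance 2W. The true variance is σ₀² + σₜ² − 2σ₀ₜ. The SE ratio (model/true) is the root of their quotient, and the actual size is 2·[1 − Φ(1.96 × ratio)].
- r = 0.4 throughout: W = 0.6; 2W = 1.2 and the true value is 1.2. Ratio 1.00, size 5% at both visits.
- Decay 0.70 per 4 weeks: correlations 0.70, 0.49, 0.168 with baseline and 0.70, 0.240, 0.343 later; mean 0.440, W = 0.560. Follow-up √(1.120/1.664) = 0.82, size 10.8%. Post √(1.120/1.020) = 1.05, size 4.0%.
- Decay 0.85 per 4 weeks: 0.85, 0.7225, 0.444 with baseline and 0.85, 0.522, 0.614 later; mean 0.667, W = 0.333. Follow-up √(0.666/1.113) = 0.77, size 12.9%. Post √(0.666/0.555) = 1.10, size 3.2%.
- Baseline less correlated with all later visits (0.50/0.40/0.40; 0.70, 0.65, 0.70 later): mean 0.558, W = 0.442. Post and follow-up √(0.883/1.2) = 0.86, size 9.3%.
- r = 0.4 with baseline SD 25% smaller: mean variance (0.5625 + 3)/4 = 0.891, mean covariance 0.35, W = 0.541. Ratio √(1.081/0.9625) = 1.06, size about 3.8% at both visits.

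**Step 3: between-arm difference at a visit, model as written.** With a single slope for baseline SPIN and the baseline row included, that slope is b = mean of (1, r₀₄, r₀₈, r₀,₂₀). The between-person residual variance of the four-visit mean is B = Var(mean) − b². The model's variance at any visit is T = (B − W/4) + W. The true variance of the adjusted score is 1 + b² − 2b·r₀ₜ. Under the protocol's r = 0.4:
- b = (1 + 3 × 0.4)/4 = 0.55
- B = 0.55 − 0.3025 = 0.2475
- T = (0.2475 − 0.15) + 0.6 = 0.6975
- true variance = 1 + 0.3025 − 0.44 = 0.8625
- ratio √(0.6975/0.8625) = 0.90, size 7.8%, the same at post and follow-up

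The same formulas under decay give:

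| Decay per 4 weeks | b | T | True, post | Size, post | True, follow-up | Size, follow-up |
|---|---|---|---|---|---|---|
| 0.70 | 0.590 | 0.652 | 0.770 | 7.1% | 1.149 | 14.0% |
| 0.85 | 0.754 | 0.431 | 0.479 | 6.3% | 0.899 | 17.5% |

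**Step 4: simulation check.** I drew 10,000 null trials per pattern, 111 per arm. The follow-up change contrast rejected 4.9% at r = 0.4, 10.5% at decay 0.70 and 13.9% at 0.85. The per-visit comparison at r = 0.4 rejected 7.4% (post) and 7.6% (follow-up); other simulations of the same contrast gave 8% to 9%. The two models proposed under the fix rejected between 4.5% and 5.6% in every pattern. The overall 3-df interaction test is only mildly affected (5% to 7% in separate runs).

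**The case against.** This is a condensed article. It does not say that participant is the only random effect, and it states no residual covariance. A full protocol or SAP may do so, and silence there is no fault. That stands as a limit on certainty. But the article lists the fixed effects exhaustively and gives the random term a stated purpose that describes an intercept. In Mediation Analyses, where more is wanted, it says that paths vary between participants. The model as published is therefore a stated choice.

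A reader might infer something stronger: that the follow-up effect certainly gets too small a standard error and the post effect too large a one, so that the post claim loses power. The documents do not support that. Their only correlation, a common 0.4, gives no distortion of the change contrasts at equal SDs. The post direction reverses if baseline correlates less with all later visits, and for the per-visit comparison the post standard error came out too small in every pattern examined (ratios 0.81 to 0.97). Nor is a smaller baseline SD documented. It is plausible from the entry cut-off, but on its own it makes the change contrasts conservative at both visits.

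It is also fair to object that simply substituting an unstructured 4×4 covariance fails. With baseline SPIN as both row and covariate, a slope of 1 makes every baseline residual zero, the baseline variance collapses and the likelihood is unbounded. The fix below allows for this.

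**Conclusion.** The point holds in conditional form. Read literally, the primary model imposes compound symmetry on unequally spaced visits, and the double use of baseline SPIN makes a common residual variance impossible.
- If correlation decays by 0.70 to 0.85 per 4 weeks, the baseline-to-follow-up contrast has a true size of about 10% to 13% instead of 5%. The decay is an assumption.
- The between-arm comparison at post and at follow-up has a size of about 8% (up to about 9% in simulation) even under the protocol's r = 0.4 with equal SDs. This part needs no assumption of decay.
- The post change contrast runs from about 3% to about 9% according to the pattern, so no direction can be asserted.

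The figures assume complete balanced data; dropout is not modelled. The sample size is not called into question. The matter should be corrected before analysis, but it does not undermine the design.

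**What to change.** In Main Analyses, choose one of two forms:
- model weeks 4, 8 and 20 as outcomes, with baseline SPIN and baseline-by-time as covariates and an unstructured 3×3 within-participant covariance; or
- keep all four visits as outcomes with an unstructured 4×4 covariance and drop the baseline SPIN covariate.

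Use Kenward-Roger degrees of freedom in either case, and name a participant-clustered robust variance as the fallback if the model does not converge. Apply the same form to the continuous secondary outcomes in Further Analyses.

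The cost is a short edit and 6 or 10 covariance parameters in place of 2, which 222 participants support easily. No data collection or sample size changes.
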